# Cost-effectiveness of the mobile application TCApp combined with face-to-face CBT treatment compared to face-to-face CBT treatment alone for patients with an eating disorder: study protocol of a multi-centre randomised controlled trial

**DOI:** 10.1186/s12888-018-1664-4

**Published:** 2018-05-02

**Keywords:** Eating disorders, mHealth, Treatment, Cost-effectiveness

## Abstract

**Background:**

The clinical utility of the existing apps for people with eating disorders (EDs) is not clear. The TCApp has been specifically developed for people with EDs, is based on the principles of Cognitive Behavioural Treatment (CBT) and allows a bidirectional link between the patient and the therapist. The objectives of the study are, first, to assess the clinical efficacy of a combined intervention for Eating Disorders (EDs) that includes an online intervention through the TCApp plus standard face-to-face CBT in comparison to standard face-to-face CBT alone, and second, to examine the cost-effectiveness of the TCApp and identify potential predicting, moderating and mediating variables that promote or hinder the implementation of the TCApp in ED units in Spain.

**Methods:**

The study methodology is that of a randomised controlled trial combining qualitative and quantitative methods, with a 6-month follow-up. Approximately 250 patients over 12 years old with a diagnosis of an ED from several ED units in Spain will be randomised to one of two different conditions. Participants, their caregivers, healthcare professionals and technical staff involved in the development and maintenance of the application will be assessed at baseline (T0), post-intervention (T1) and at 6 months follow-up (T2). Primary outcome measures will include ED symptomatology while secondary measures will include general psychopathology and quality of life for patients, quality of life and caregiving experience for family caregivers and adoption-related variables for all participants involved, such as perceived usability, user’s satisfaction and technology acceptance. For the cost-effectiveness analysis, we will assess quality-adjusted life years (QALYs); total societal cost will be estimated using costs to patients and the health plan, and other related costs.

**Discussion:**

The study will provide an important advance in the treatment of EDs; in the long term, it is expected to improve the quality of patient care and the treatment efficacy and to reduce waiting lists as well as direct and indirect costs associated with the treatment of EDs in Spain.

**Trial registration:**

ClinicalTrials.gov: NCT03197519; registration date: June 23, 2017.

## Background

In the last three decades, Eating Disorders (EDs) have become a particularly relevant public health concern due to their growing incidence, the severity of the associated physical and psychiatric comorbidities [1], the high suicide and mortality rates [2] and the resistance of patients to treatment [3], among other reasons. In addition, they constitute today the third most prevalent chronic illness among the adolescent female population in developed and westernized societies and a public health priority around the world [4, 5]. Specifically in Spain, 75,000 adolescents are affected by one of the different manifestations of the disorder, among which 90% are female [6].

Although we do not have specific data related to the economic burden of treatment in Spain, various Cost Of Illness (COI) studies conducted in other European countries indicate that the direct costs for diagnosis and treatment of patients (medical expenditures, nonmedical costs, out-of-pocket expenses of the patient and his/her family), together with the indirect costs (loss of productivity due to sickness, reduced productivity or death) imply a high economic impact [7] and a significant loss of quality of life for people affected [8, 9] and their families [10]. However, according to the systematic review conducted by Stuhldreher et al. (2012), COI studies are sparse, the costs are often underestimated, the majority target only outpatient settings, and due to their heterogeneous nature, it is impossible to carry out comparisons between studies.

The widespread use of new technologies offers a promising and innovative way to improve the quality of care for patients with an ED and to reduce its economic burden. Systematic reviews of the literature demonstrate the effectiveness of eHealth as a complementary therapeutic tool in the treatment of EDs [11–16]. For example, Internet-based interventions have proved their efficacy in reducing ED-related symptoms in a number of Randomised Controlled Trials (RCTs) [17–19]. However, to date, there is a complete absence of RCTs evaluating the effectiveness of mHealth interventions for EDs and existing studies only offer preliminary results about acceptability and usability of such tools [20–22].

In particular, mHealth interventions for EDs may help patients to increase their treatment adherence and to better deal with feelings of stigma associated with face-to-face psychological treatment. Additionally, considering the shortage of ED specialists and the long waiting lists in mental health outpatient settings, mHealth interventions may offer improved accessibility and availability of treatment, at lower costs [20].

In addition, it is worth noting that traditional Cognitive Behavioural Therapy (CBT) is considered the “gold standard” treatment for EDs. CBT uses real-time self-monitoring of patients’ eating habits and behaviours to help them gain a clearer picture of their problem and understand what triggers their behaviour and what are the consequences of it. Self-monitoring is the key driver of behavioural change as it helps patients intervene in the moment [12]. By doing so, all the relevant information regarding the eating problem is entered in real time and can be recovered repeatedly when the therapists or the patients want. Although the efficacy of online CBT interventions as alternatives to face-to-face treatment for patients with EDs is rather controversial [13, 23], such interventions may have a lot of advantages when used as therapeutic tools. Within this context, smartphone apps can offer an attractive and personalised treatment option and can reach a wider range of patients with low motivation for change or others who desire anonymity. Self-monitoring could be enhanced through smartphone-based interventions, as data entry is simpler than traditional pen-and-paper methods. In addition, reminders and motivational messages as well as bidirectional interactions between patient and therapist can improve adherence to treatment [24].

Nevertheless, while growth in mHealth interventions has been rapid, advances in the existing evaluation frameworks have not been seen [25–27]. As a result, a huge number of health apps are widely available to the general healthcare public without possessing best-practice guidelines and certifications or a standardised validation process to assess their long-term cost benefits [28].

The TCApp^1^ represents a tool for connecting patients and therapists in the time between medical consultations. It is currently available on Google Play and Apple Store markets, there are more than 412 patients who are currently using it and has been developed in collaboration with different public and private mental health institutions in the Barcelona area (Althaia, Hospital de Sant Rafael, CST, ITA and Hospital Sant Joan de Déu). The TCApp was designed from the very beginning with therapists’ and patients’ needs and interests in mind. By using the TCApp, patients and therapists are in continuous contact, allowing for a quicker reaction from the therapist according to the patients’ needs.

Through the TCApp, patients can record their thoughts, actions, emotions and whatever the therapists consider relevant for the therapy, since the app can be customized according to the therapy requirements of each specific patient. It involves algorithms based on artificial intelligence that can generate alarms when strategic words (i.e. suicide, death, etc.) are written. It also introduces technologies to allow real-time online contact with therapists and gamification aesthetics with prizes, rewards and reminders to improve patients’ engagement.

The back-office tool for therapists is a web-based platform where therapists can see in real time what their patients have registered (i.e. generation of graphs in a period of time to see parameter comparison and patient evolution) and they can interact in real time with them, using PUSH notifications. The tool is integrated in Azure server in order to ensure accordance with the most restrictive data protection laws and it is prepared for the integration in local management systems of hospitals and clinics. Lastly, there is currently no application available to provide the same services and benefits as the TCApp as most of the available applications contain self-help functionalities, rather than allowing for a bidirectional link between the patient and the therapist.

The purpose of this trial is to conduct a multicentre, randomized controlled trial with 250 patients diagnosed with an ED. In this experiment, the patients from the experimental group will test a mHealth application (TCApp developed by HealthApp) and then, a clinical efficacy analysis and economic evaluations will be performed. To do this, we have set the following three specific objectives:To evaluate the clinical efficacy of an intensive intervention that includes both standard face-to-face Cognitive Behavioural Treatment (CBT) (treatment as usual, TAU) plus mHealth intervention using the TCApp, versus the TAU alone.To carry out an economic evaluation of the new mHealth intervention and identify factors that promote or hinder the implementation of the TCApp in mental health settings in Spain.To analyse the adoption processes of this type of applications by patients and health professionals and identify the determinants of mHealth adoption.

The implementation of the intensive intervention program (TAU + TCApp) would result in a more significant improvement of the ED symptoms compared to the TAU control group. More specifically:The application of the intensive mHealth intervention would lead to significantly greater change scores (difference between T0 and T1, which will be also maintained at follow-up, T2) in the primary outcome variable of ED psychopathology, compared to the control group.The mHealth intervention would lead to significantly greater change scores (difference between T0 and T1, which will be also maintained at follow-up, T2) in patients’ secondary outcome variables: a) depression symptoms, b) anxiety symptoms, c) readiness to recover, d) suicidal risk, and e) quality of life, compared to the control group.Similarly, intensive intervention would result in greater change scores (difference between T0 and T1, which will be also maintained at follow-up, T2) in caregivers’ variables: a) quality of life and b) caregiver burden.

## Methods

### Design

We will follow a mixed-methods approach, combining quantitative and qualitative methods, through a multi-centre RCT with two parallel groups (an intensive intervention group with TAU and TCApp and a TAU control condition) with a 1:1 allocation.

### Sample

The total sample will be approximately 250 patients with a diagnosis of EDs who are currently under treatment, from different public and private mental health services in Spain (Parc Taulí Hospital, Sant Rafael Hospital, Servei de Salut de les Illes Balears, Sant Joan de Déu Hospital, Niño Jesús University Children’s Hospital, San Carlos Clinic Hospital, Dexeus University Hospital of the Quirónsalud group and Eating Disorders Institute ITA).

All patients will receive a standard CBT treatment, counting with the support of a multidisciplinary team of the different ED units (psychiatry, psychology, nutrition, nursing).

#### Inclusion criteria

Diagnosis of an Eating or Feeding Disorder, based on: a) the Schedule for Affective Disorders and Schizophrenia-Present and Lifetime version (K-SADS-S-PL) (DSM-V criteria) [29] for minor patients or b) the Structural Clinical Interview for DSM-IV (SCID-1) [30] for adult patients. The diagnosis should be one of the following types: Anorexia Nervosa (AN); Bulimia nervosa (BN); Binge Eating Disorder (BED); Other Specified Feeding or Eating Disorder: Atypical Anorexia Nervosa, Bulimia nervosa (of low frequency and/or limited duration), Binge-eating disorder (of low frequency and/or limited duration), purging disorder, night eating syndrome.Treatment regimen: Day Hospital or Outpatient treatment, regardless of the illness duration or the severity of the disorderTreatment received by ED unit of reference: Standard Cognitive Behavioural TherapyUnderstanding of Spanish, Catalan or English language, depending on the language option chosen by the participant for the TCAppMinimal digital skills and availability of proper mobile phone for patients

#### Exclusion criteria

Age less than 12 yearsTreatment regimen: Inpatient treatmentDiagnosis of psychosisIntellectual disabilityHave a mobile phone with a Windows Phone operating system

### Procedure and randomization

First, all material with information related to the study (research protocol, informed consent, patient information sheet, Data Collection Logbook, safety- and privacy-related issues concerning the TCApp) have been submitted for approval to each one of the Ethical Committees of the participating hospitals. It should be mentioned that the approval of the Ethical Committee of the University leading the study (Open University of Catalonia, UOC) was obtained on February 21st, 2017.

Participants will be recruited after previous recommendation by one of the ED specialists working at each centre. Specialists will do a preliminary screening following the inclusion and exclusion criteria in order to identify potential candidates for the study. Interested individuals will be able to confirm their participation by notifying the ED specialist who will be responsible for their treatment. Then, an information letter and an informed consent form will be delivered to them.

After completing and signing these documents (for underage patients, their parents will be required to sign the informed consent and for patients aged more than 18 years, they will have to sign informed consent themselves), initial clinical interviews will be conducted by psychologists or other collaborators working in the ED unit. All interviewers will be previously trained in administering the K-SADS-PL or SCID interview, depending on the participant’s age. The objective of these interviews is: a) to determine whether participants are definitely eligible for the study following the inclusion criteria, b) to establish the diagnosis for each patient and c) to evaluate them for possible comorbidities. At this time, sociodemographic and clinical data of each patient will also be collected through a brief interview. Then, those who meet the inclusion criteria will be invited to complete the baseline questionnaires for the study. During this baseline evaluation (T0), questionnaires will be administered to patients, their informal caregivers and the ED specialist responsible for the online monitoring of each patient. In addition, telephone interviews will be conducted with the technical staff and the ED specialists.

After completion of the baseline questionnaires, participants will be randomized to one of the two study conditions (experimental or control group). Randomization will be carried out by an independent researcher in blocks of 10 participants within each ED unit (50% of patients from each block will be assigned to the experimental group and the other 50% to the control group), using a random allocation program. Allocation concealment will be also ensured.

After this, patients will be notified about the group they belong to during their next visit to the ED unit. At this time, patients from the experimental group will be given oral and written instructions about how to download and use the TCApp. ED specialists responsible for the online monitoring will be also taught the basic principles for using the application. In turn, patients from the TAU control group will be told that access to the TCApp will be offered to them after a waiting period of 6 months (T2 evaluation completed).

Then, each group of patients will receive the treatment that corresponds to them during a period of 12 weeks. At the end of the 12-week treatment, patients from the experimental group will stop using the TCApp and the evaluation post-treatment (T1, 12 weeks later) will be carried out, including: a) a brief clinical interview (patients), b) questionnaires (patients, informal caregivers, ED specialists); c) telephone interviews (technical staff, ED specialists) and d) focus groups with ED specialists of each institution who are interested in participating as well as with patients of the experimental group.

In the follow-up evaluation T2, 6 months after the beginning of treatment, patients, their informal caregivers and ED specialists responsible for the online monitoring will complete some questionnaires. In addition, telephone interviews will be conducted with ED specialists and a brief clinical interview will be carried out with patients. At the end of this phase, patients from the control group will be given access to the TCApp after being contacted by the ED specialist who will be responsible for their online monitoring.

Figure 1 presents the procedure and the timeline of the study and Table 1 provides a detailed description of the methodology with a definition of the study variables and their assessment tools.

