### Study conditions

The experimental group will receive the standard treatment based on CBT principles that is offered by the different ED units in Spain, plus an online intervention using the TCApp for a period of 12 weeks. Only one ED specialist will be responsible for the online monitoring of each patient. For the specific purposes of our study, this role has been assigned to the nursing staff for most of the centres.

The TCApp application proposes patients a series of different functionalities, including daily self-records of their thoughts, emotions and actions, a chat with their therapists and motivational exercises. An online platform of the TCApp (BackOffice) is also available for therapists for the online monitoring of each patient. There, therapists have the possibility to follow the patient’s daily self-records, generate personalized reports and graphs and communicate with him/her via chat, based on the information that the patient has provided online.

During these 12 weeks, the patient should use the TCApp at least once a day, completing at least one self-record per day and/or contacting his/her therapist via chat when needed. The therapist responsible for the online monitoring should connect to the online platform and perform the following actions at least once a week: follow the patient’s daily self-records, generate personalized reports or graphs and communicate with him/her via chat. After a 12-week period, patients from the experimental group and their therapists will stop using the TCApp (they will be discharged).

The TAU control group will receive the standard face-to-face CBT, offered by the different ED units in Spain. Patients from the control group will be offered access to the TCApp after a 6-month period.

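### A single published block size of 10 within each unit, with no masking described, lets a staff member holding a full, current tally foresee up to one allocation in six; randomly varied, undisclosed sizes would cheaply remove most of this

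*Protocol article*

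**What the plan says.** All references are to the Methods of the protocol article.

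- **Block scheme** (Procedure and randomization): "Randomization will be carried out by an independent researcher in blocks of 10 participants within each ED unit", and "50% of patients from each block will be assigned to the experimental group and the other 50% to the control group". The Design section gives the overall ratio as "with a 1:1 allocation". One block size is stated, and nothing suggests that it varies.
- **Concealment** (same section): "Allocation concealment will be also ensured". The list is produced with a random allocation program, and randomisation follows the baseline questionnaires.
- **Who puts patients forward** (same section): "Participants will be recruited after previous recommendation by one of the ED specialists working at each centre". These specialists also do the preliminary screening, and "initial clinical interviews will be conducted by psychologists or other collaborators working in the ED unit". All of this comes before randomisation.
- **How arms become known** (same section): "patients will be notified about the group they belong to during their next visit to the ED unit". App patients then receive instructions, and controls are told that they will wait 6 months for access. Study conditions has one ED specialist monitor each app patient online, and "this role has been assigned to the nursing staff for most of the centres". No masking of patients or unit staff is described.

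**The concern.** With a fixed block of 10 and exact 5:5 balance, once five patients in a block have gone to one arm, every remaining place in that block must go to the other. The list can be perfectly hidden and this still follows from counting past allocations, because the size and the balance are printed in a public article. The people who decide which patient to put forward next work in the same unit where those past allocations come to light.

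The stake is selection bias. A person who knows the next arm could bring forward or hold back a patient who seems motivated, at ease with an app, or less severely ill. The primary measures (EDE-Q and SEED) are self-reported questionnaires and the planned effect is small (d = 0.40), so even a modest imbalance in prognosis would count. Adjustment in the analysis could correct only for characteristics that were measured.

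**Working it through.** The article gives no predictability figure, so there is none to reproduce.

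**Inputs**
- Block size 10, five per arm, separately within each unit (Procedure and randomization).
- 250 patients and d = 0.40 (Sample size calculation).
- Eight named services (Sample). Equal recruitment across them is an assumption.
- Prognosis shift of 0 to 0.5 SD between patients steered towards a foreseen app place and those steered towards a foreseen control place. This is an assumption; nothing in the article anchors it.

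**1. Certain allocations with a complete, current tally.** There are C(10,5) = 252 equally likely blocks. The last k places are all forced to one arm, or are the first of such a run, in 2 × C(10−k, 5) of them:

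| Place in block | k | Blocks in which it is certain | Probability |
|---|---|---|---|
| 10th | 1 | 252 | 100% |
| 9th | 2 | 112 | 44.4% |
| 8th | 3 | 42 | 16.7% |
| 7th | 4 | 12 | 4.8% |
| 6th | 5 | 2 | 0.8% |

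The sum is 420/252 = 1.67 per block, or 16.7%. The closed form 2m/(m+1) with m = 5 gives the same: 10/6 = 1.67.

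**2. In this trial.** Complete blocks throughout would give 250/6, about 42 allocations. With eight equal units of 31 or 32 patients, each unit has three complete blocks, and the first two places of a fourth block are never certain. That gives 24 × 1.67 = 40 of 250, or 16.0%. With other assumed numbers or sizes of units the share is about 10% to 17%.

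**3. Effect of delayed notification.** If the latest d allocations in the unit are not yet known, the first d rows of the table drop out of the sum:
- d = 1: (112 + 42 + 12 + 2)/252 = 0.67 per block, 6.7%.
- d = 2: (42 + 12 + 2)/252 = 0.22 per block, 2.2%.
- d = 3: (12 + 2)/252 = 0.056 per block, 0.6%.

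**4. Possible bias, acting only on certain allocations.** Bias = certain share × prognosis shift.
- Full tally: 0.167 × (0 to 0.5) = 0 to 0.08 SD. The top end is 0.083/0.40, about 21% of the planned effect.
- One allocation unrevealed: at most 0.067 × 0.5 = 0.03 SD.
- Two unrevealed: at most 0.022 × 0.5 = 0.01 SD.

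**5. Best-guess rate.** Always guessing the under-filled arm is right in m + 2^(2m−1)/C(2m,m) − 0.5 = 5 + 512/252 − 0.5 = 6.53 of 10 allocations, or 65.3%.

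**6. After the change.** Simulation of 31 patients per unit, with a full tally and an optimal guesser who knows the set of possible sizes but not the realised ones:

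| Blocks | Certain | Best guess correct |
|---|---|---|
| Fixed 10 | 16.2% | 64.8% |
| Random 6, 8, 10, 12 | 1.0% | 64.6% |

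The top of the bias range in step 4 becomes 0.01 × 0.5 = 0.005 SD.

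**The case against.** Several counter-arguments have force.

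*One in six overstates what anyone in a unit would know.* This stands. A patient is recommended, screened, consented, interviewed and assessed at baseline before being randomised, and the arm is disclosed only at the next visit. Recent allocations may therefore be unknown when the next patient is put forward, and step 3 shows how quickly the certain share then falls.

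*No one person is shown both to choose patients and to see every allocation.* This also stands. Recommendation lies with one of the specialists, interviews with psychologists or other collaborators, and monitoring mostly with nurses. A reader might infer that the specialists see each allocation in their unit; the article does not say so. It shows only that arms become known to people working there.

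*The design already has safeguards.* In part. An independent researcher, an allocation program, randomisation after baseline and a promise of concealment protect the list. They do not stop deduction from known past allocations. Nor is 10 a small block: fixed blocks of 4 or 6 would make 33% or 25% of allocations certain. The weakness is that the size is fixed and disclosed.

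*The blocks might be randomised ten patients at a time.* If ten consented patients were allocated together, nothing would be predictable. The article does not say that this is done.

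*The change does nothing against guessing.* Correct. A reader might apply a prognosis shift of 0.2 to 0.5 SD to the 65% best-guess rate and reach a bias of about 0.06 to 0.15 SD, or 15% to 38% of the planned effect. That would require staff to act on every weak guess, and the shift has no basis in the article. Varying the block sizes would also leave that figure almost unchanged, so it cannot serve as the argument for the change.

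**Conclusion.** The point holds as a minor one. The stated scheme leaves an avoidable route to foreknowledge that the concealment sentence does not close. Its size is at most 17% of allocations known with certainty, conditional on a staff member keeping a complete and current tally over full blocks. A realistic figure is probably lower, though the article does not allow it to be fixed. The corresponding bias is at most about 0 to 0.08 SD, on the assumed shift of 0 to 0.5 SD and on action being taken only when the next arm is certain.

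A reader might infer that the design actually makes one allocation in six predictable, or that the result will be biased. The documents support neither: the first needs the full tally, and the second needs someone to use it.

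**What to change.** The independent researcher should generate the list with randomly varying permuted blocks within each unit, for example 6, 8, 10 and 12, and should not disclose the sizes to the units. Where a unit is already recruiting, the switch can be made at its next block boundary. The stated purpose should be to reduce allocations that are certain; it should not be presented as protection against guessing.

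The cost is one setting in the allocation program and slightly looser balance of arms within units. Stratification by unit and the 1:1 ratio are kept.
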